#### Projected quit rates

As defined in the 2012 Cochrane review of smoking cessation in hospitalized patients [35], across both study arms, smokers who receive post-discharge support and medications will receive level-4 intensity treatment and smokers who receive only inpatient brief counseling will receive level-1 intensity treatment. Pooled quit rates are 10% for level-1 intensity studies and 29% for level-4 intensity studies [35]. Based on EQUIP and other trials, we estimate that 30% of OPT-IN participants will be ready to quit and receive services [36, 37]. For OPT OUT, based on the Inter99 trial and our pilot study on proactive quitline counseling we estimate that 80% of patients will accept services [38, 39]. We calculate the proposed quit rates within each condition using the following formula:$$ \left[\left(\mathit{\mathsf{prop}}.\mathit{\mathsf{receivingservices}}\times \mathit{\mathsf{level}}\ \mathit{\mathsf{4}}\ \mathit{\mathsf{quitrates}}\right)+\left(\mathit{\mathsf{prop}}.\mathit{\mathsf{not}}\ \mathit{\mathsf{receivingservices}}\times \mathit{\mathsf{level}}\ \mathit{\mathsf{1}}\ \mathit{\mathsf{quitrates}}\right)\right]. $$

We estimate the quit rate to be 15.7% in the OPT-IN group: [(.30 × .29) + (.70 × .10)] = .157. We estimate the quit rate to be 25.2% in the OPT-OUT group: [(.80 × .29) + (.20 × .10)] = .252.

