Hypothesis 1: compared to OPT IN, significantly more patients in OPT OUT will participate in counseling, use cessation medications, and be abstinent from smoking	Abstinence: treatment condition and 1-month 7-day point-prevalence abstinence	2-sample binomial test
	Counseling: treatment condition and total counseling time by 1 month	2-sample lognormal test
	Medication: treatment condition and number of days of medication use	2-sample Poisson test
Hypothesis 2: significantly more smokers in OPT OUT will be abstinent from smoking, and mediation analyses will partially or fully explain the effects	Treatment condition and 6-month and • 7-day point-prevalence abstinence • Default variables • Counseling/medication use	Bayesian structural equation modeling with a logistic outcome
Hypothesis 3: OPT OUT will be more costly but also more effective than OPT IN	Treatment condition and 1-month abstinence • Variable costs	Incremental cost/quit

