#### Analyses by aim

The main analyses for each aim are outlined below (Table 5).

Aim 1. Hypothesis 1: among patients consented into the trial, significantly more patients in OPT OUT will participate in counseling, use cessation medications, and be abstinent from smoking at 1 month post randomization compared to OPT IN. These analyses will involve two-sample tests.

Aim 2. Hypothesis 2: significantly more smokers in OPT OUT will be abstinent from smoking, and mediation analyses will find that counseling participation, medication use, and default-theory-based variables will partially or fully explain the effect of OPT OUT on cessation at 6 months post randomization. After identifying a structural equation model that adequately fits the data for the hypothesized associations between the intervention and 6-month outcome, i.e., that Comparative Fit Index (CFI) > .9 and Root Mean Square Error of Approximation (RMSEA) < .8, we will examine mediation using approaches based on the work of MacKinnon et al. [49], Brown [50], and Shrout and Bolger [51]. Our theoretical model (Fig. 1, Significance) will guide our analysis.

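### The 6-month superiority clause of Hypothesis 2 is tied only to a mediation model, with no 6-month arm comparison and no statement of which effect decides it

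*Protocol article*

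**What the plan says.** Table 5 states the hypothesis as "Hypothesis 2: significantly more smokers in OPT OUT will be abstinent from smoking, and mediation analyses will partially or fully explain the effects". The variables in that row are treatment condition, 6-month point-prevalence abstinence, the default variables, and counseling and medication use. The strategy in that row is "Bayesian structural equation modeling with a logistic outcome".

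Under Analyses by aim, Aim 2 repeats the superiority clause and says the mediators "will partially or fully explain the effect of OPT OUT on cessation at 6 months post randomization". The procedure begins "After identifying a structural equation model that adequately fits the data for the hypothesized associations between the intervention and 6-month outcome", with limits on CFI and RMSEA, and then turns to mediation.

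Hypothesis 1 is handled differently. Table 5 gives 1-month abstinence a two-sample binomial test, and Aim 1 says "These analyses will involve two-sample tests". The binomial posterior under Bayesian design is also for the 1-month endpoint.

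The expected effect is built under Projected quit rates: "Pooled quit rates are 10% for level-1 intensity studies and 29% for level-4 intensity studies". These two rates are applied unchanged in both arms. Only the share receiving services differs, at 30% in OPT IN and 80% in OPT OUT.

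**The concern.** The two parts of Hypothesis 2 have different nulls. The first part's null is equal 6-month abstinence in the two randomized arms. A model containing the mediators offers three quantities:

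- **Direct path:** the arm difference at fixed services and perceptions.
- **Indirect path:** the part carried by the mediators.
- **Total effect:** the two combined.

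Only the total effect addresses the first null, and it does so only if the model keeps the direct path. The article names none of the three as deciding. It also does not require the direct path to be kept, since the model is the one found to fit adequately and full mediation is an anticipated result.

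Abstinence at 6 months is the trial's only longer-term effectiveness result. As the text stands, the answer could turn on the choice of path, the choice of mediators and a fit criterion. Randomization protects none of these.

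**Working it through.** **Inputs.** From Projected quit rates: services 30% (OPT IN) and 80% (OPT OUT); quitting 29% with services and 10% without. From Power, sample size, and trial duration: average size 625 with 387 in OPT OUT, hence 625 − 387 = 238 in OPT IN; maximum size 1000, taken here as 500 per arm. Assumptions: the same rates at 6 months (the article gives no 6-month projection), one binary mediator, no missing data, two-sided 5% level.

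**1. The article's own figures.**
- OPT IN: 0.30 × 0.29 + 0.70 × 0.10 = 0.157.
- OPT OUT: 0.80 × 0.29 + 0.20 × 0.10 = 0.252.
- Difference: 0.095. Both rates reproduce exactly.

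**2. Direct path under that projection.** Given services, quitting is 29% in either arm; without services it is 10% in either arm. The arm log odds ratio given services is therefore exactly 0. The marginal log odds ratio is ln(0.252/0.748) − ln(0.157/0.843) = −1.088 + 1.681 = 0.593.

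**3. Power of a plain two-arm comparison.** Power = Φ[(0.095 − 1.96·SE0)/SE1], with SE0 pooled and SE1 unpooled.
- 500/500: SE0 = √(0.2045 × 0.7955 × 2/500) = 0.02551; SE1 = √[(0.1324 + 0.1885)/500] = 0.02533; power = Φ(1.78) = 96.2%.
- 238/387: pooled rate 0.2158; SE0 = 0.03389; SE1 = √(0.1324/238 + 0.1885/387) = 0.03230; power = Φ(0.885) = 81.2%.

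**4. Simulation under the projection.** Arm sets services, services set quitting, and there is no direct effect. The table gives the share of trials favouring OPT OUT.

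| Quantity read | 238/387 | 500/500 |
|---|---|---|
| Two-arm comparison | 80.1% | 96.4% |
| Direct (arm) path, services in model | 2.2% | 2.0% |
| Total effect, model keeps arm path | 79.5% | 96.1% |
| Indirect path | 99.9% | about 100% |

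Separate runs put the direct path at 2-4% and the two-arm comparison at 80-82% and 95-96%.

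**5. The opposite error: the arms do not differ.** Assume 30% are ready to quit, all ready patients accept services in both arms, and quitting depends only on readiness (29% v 10%). Both arms then quit at 0.30 × 0.29 + 0.70 × 0.10 = 15.7%.
- OPT IN: served 29%, unserved 10%.
- OPT OUT: served (0.30 × 0.29 + 0.50 × 0.10)/0.80 = 17.1%, unserved 10%.

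Drop the arm path, so that the model's OPT OUT effect is the difference in service uptake times the pooled service-quit difference:
- 500/500: served (150 × 0.29 + 400 × 0.17125)/550 = 20.4%; effect 0.50 × (0.204 − 0.10) = 5.2 points.
- 238/387: served (71.4 × 0.29 + 309.6 × 0.17125)/381 = 19.4%; effect 0.50 × (0.1935 − 0.10) = 4.7 points.

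The true effect is zero. In simulation this model shows an effect in 87-99% of trials across the two sizes, against 2-3% for the two-arm comparison. The indirect path of a model that keeps the arm path is positive in 94% (238/387) and 100% (500/500).

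**The case against.** The strongest reply is that nothing in the article says the direct path decides. A reader might infer that a real 9.5-point difference at 6 months would be missed. The documents do not support that. The mediators are to explain the effect of OPT OUT partially or fully, so the effect to be explained is the total effect, and a zero direct path is an allowed result that is compatible with superiority. Step 4 shows that the total effect from a model keeping the arm path loses less than 1 point of power against the two-arm comparison. The 9.5 points also belong to the 1-month endpoint.

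A similar caution applies to the false-positive scenario. No passage judges superiority by the indirect path. The scenario makes services inert, contrary to the projection, and it leaves out baseline readiness, which Table 3 collects. With readiness in the model and measured without error, the indirect false-positive rate falls to about 3%. The fit criterion is also placed before mediation and is not stated as a condition on an arm comparison.

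All of this narrows the point. It does not remove it. A fuller analysis plan may settle the matter, but Table 5 is not silent: it names a method for the superiority clause, and that method does not by itself answer it. No separate arm comparison exists at 6 months for the fit criterion to leave untouched.

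**Conclusion.** The point holds as an unresolved choice of decision quantity with material consequences, and not as a demonstrated loss of the effect. The 6-month superiority clause rests on one mediator-containing model selected by fit, with no deciding effect stated. With the projection's structure carried to 6 months, the chance of a positive finding runs from about 2-3% (direct path) to about 80% or 96% (total effect or two-arm comparison, by sample size). If the arm path is dropped and readiness drives both uptake and quitting, a null difference can appear positive in 87-99% of trials. The zero direct path follows from the projected structure whatever the rates; the percentages depend on the assumptions listed with the inputs. The 1-month primary analysis is unaffected.

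**What to change.** Split Hypothesis 2 in Table 5 and in Aim 2 under Analyses by aim.

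1. Judge the superiority clause by verified 6-month abstinence compared by randomized arm in all randomized patients, with no mediators in the model. Use the same binomial posterior and missing-as-smoker rule as at 1 month. Report the risk difference with its interval and the posterior probability that OPT OUT exceeds OPT IN.
2. State that this comparison does not depend on CFI or RMSEA.
3. Use the structural equation model only to decompose that effect.

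The cost is a change of wording and one further comparison on data already being collected. No extra patients or visits are needed.

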#### Accrual (enrollment) patterns

Accrual patterns refer to how rapidly we enroll patients in the trial. These are important to Bayesian adaptive designs for determining the length of the trial. Based on accrual patterns for EQUIP and other hospital studies conducted by our team, and the sample size required for this trial, we assume that the accrual patterns will follow a Poisson distribution with an average of 6.7 patients per week.

#### Accounting for missing data

For the main outcome analysis, in accordance with the ITT principle, patients lost to follow-up will be considered smokers. We will also calculate main and secondary outcomes using imputed data. Missing observations on covariates will be handled through Bayesian posterior predictive distributions with auxiliary variables, auxiliary variables are variables that are not part of the analysis model, yet are included as missing data correlates to strengthen the assumption that missing covariates are missing at random (MAR; missingness is independent of the missing value) [40–42]. Assuming data are MAR, analyses employed under the ITT principle are considered acceptable.

#### Sensitivity analyses

To explore the effects of assuming MAR when data are actually MNAR (missing not at random) sensitivity analyses will be conducted using either a pattern mixture model or a selection model approach [42–45]. In addition, we will conduct and report an exploratory pooled ITT analysis to examine the effects of the Zelen design by calculating overall quit rates assuming patients who were dropped from the study due to failure to provide consent were (a) smokers, (b) nonsmokers, or (c) MNAR.

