#### Rationale for measuring main outcome at 1 month post intervention

The present study is focused on how best to engage smokers in tobacco-cessation treatment (i.e., counseling and medications) and quit. Assessing outcomes at 1 month will best capture the immediate impact of OPT IN versus OPT OUT on medication/counseling use, quit attempts, and abstinence [25, 26]. Moreover, assessing outcomes at 1 month is in accordance with Joint Commission Guidelines and UKanQuit standard practice for post-discharge follow-up of hospitalized smokers [27]. Perhaps most importantly, 1 month represents an important timeframe for hospitals, as hospitals with excessive 1-month readmission rates for selected diagnoses will receive decreased Medicare reimbursements [28]. Should our intervention prove effective, it could pave the way for future studies on the impact of smoking cessation on reduced 30-day readmission rates for specific diagnoses. Those who refuse consent at 1 month will not be eligible for inclusion again into the trial and they will be included (simply counted as smokers, because we will have no data on them) in our simplified intent-to-treat (ITT) analyses.

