#### Bayesian design

We will perform a prospective randomized comparative effectiveness *Bayesian adaptive design study* [34]. Our endpoint is the percentage of patients with verified cessation at 1 month (4 weeks) post randomization. We will perform our first planned interim analyses when we have endpoint data on 400 patients. The arm that appears to be performing the best will get more participants allocated to it in the subsequent randomization period. A new adaptive randomization structure will be updated every 13 weeks, using up-to-date outcome data, until the trial meets success or all 1000 subjects are consented. The main outcome analysis will use an ITT approach, with the denominator being all participants randomized to the study. Data from patients we are unable to reach at 1 month will be de-identified and included in data analyses.

For this study the primary endpoint is modeled:
*S*
_*QjT*_|*n*
_*jT*_ ~ Bino(*n*
_*jT*_
*,θ*
^*Q*^
_*j*_) quitting.

In addition, we provide “weakly informative” priors:logit(*θ*
^*Q*^
_*j*_) ~ N(0,100^2^).

Using the endpoint data and the prior probabilities, we then use Markov Chain Monte Carlo computations to obtain the Bayesian posterior distributions for the endpoint (i.e., quitting). We will stop randomizing into the comparative trial if the probability of a study arm having maximum utility is greater than 0.9925. The arm having the maximum quit rate is *M*
_*T*_ = max(*θ*
^*Q*^
_*1,*_
*θ*
^*Q*^
_*2*_). The stopping rule is mathematically *P*(*M*
_*T*_ > .9925). If a maximum arm is not identified after 500 patients, this procedure and accrual will continue until a maximum arm is identified or we enroll all 1000 patients. It is possible that we will reach the maximum utility criterion before 1000 patients are consented. Should this occur, we will stop the trial and begin outcome, cost, and mediation analyses in order to quickly disseminate findings.

After the maximum arm probability is evaluated, the next round of patients is randomized using a formula that favors the arm with the maximum quit rate, thus taking advantage of the information gained from our interim analyses. Using this formula, each arm is allocated for the next patients to be enrolled in the *j*
^th^ arm proportional to:$$ {V^{\ast}}_j=\mathrm{sqrt}\Big(\Pr \left({M}_{jT}={\theta^Q}_1\Big)\mathrm{Var}\left({\theta^Q}_1\right)/\left({n}_{jT}+1\right)\right). $$

This type of allocation has more desirable properties than simply using Pr(*M*

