## Discussion

### Research contribution

Missed opportunities for providing medications and counseling for tobacco dependence has created a large treatment gap. This study innovatively reframes the rationale for this gap: what if low rates of treatment are caused *not* by smokers’ lack of motivation to quit, but by requiring patients to opt in to care? Viewed from this perspective, the effects of screening for readiness on tobacco-cessation treatment can be tested by changing the way that treatment is offered. This study also identifies a major rate-limiting step in access to tobacco-cessation treatment. Regardless of what population, setting, or approach is used to disseminate tobacco-cessation treatment, as long as providers screen for readiness, the majority of smokers will report that they are *not* ready to quit—and that they will *not* receive medications or counseling.

The modified Zelen design is a novel feature of this trial, which will permit a true population-based study in which all smokers, regardless of their level of motivation, will be included in the study. By consenting patients after random assignment and treatment, the study does run the risk of dilution bias introduced by participants refusing consent post randomization [22]. A recent comprehensive review of Zelen trials found that most trials experience low dilution bias (single-digit percentages of refusal to consent or crossover). This suggests that the potential for recruiting a more representative and generalizable sample greatly outweighs the dilution bias introduced at the time of consent.

The Bayesian adaptive design approach is another novel feature of this trial. It is a highly efficient and ethical strategy for comparative effectiveness clinical trial design because it allocates more patients to effective treatments and can answer the research question earlier than conventional designs [57, 58]. In this approach one primary endpoint is used to drive the adaptive randomization. This endpoint is compared across study groups periodically, and more patients are randomized to the stronger arm until a predetermined probability that one arm has “maximum utility” is reached, which signals the end of the comparative trial.

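### The all-smokers and all-nonsmokers scenarios for consent refusers do not bound the treatment effect, and no scenario lets refusers' outcomes differ by arm

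*Protocol article*

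**What the plan says.** Consent is sought at the close of the 1-month call, after the arm-specific treatment and after smoking status has been asked (Month-1 call for service data collection and informed consent). For the main analysis, those who refuse are not left out: "they will be included (simply counted as smokers, because we will have no data on them) in our simplified intent-to-treat (ITT) analyses". The Bayesian design section sets the main analysis as intention-to-treat, "with the denominator being all participants randomized to the study".

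The Discussion (Research contribution) accepts that "the study does run the risk of dilution bias introduced by participants refusing consent post randomization", and takes comfort from a review in which most trials of this type had single-digit percentages of refusal or crossover.

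The Sensitivity analyses section has two parts. First, for data missing not at random, "sensitivity analyses will be conducted using either a pattern mixture model or a selection model approach". Second, and separately, there is an "exploratory pooled ITT analysis to examine the effects of the Zelen design". Its method is given as "calculating overall quit rates assuming patients who were dropped from the study due to failure to provide consent were (a) smokers, (b) nonsmokers, or (c)", the last being MNAR. No scenario is described by arm.

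**The concern.** Patients decide on consent knowing how they were treated and whether they stopped smoking. Both can differ by arm, so the refusers in OPT OUT may be a different kind of patient from the refusers in OPT IN. The check on the consent design should therefore ask what happens to the comparison if refusers' quit rates differ between arms.

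The two computable scenarios do not ask this. Scenario (a) is the rule already used in the main analysis. Scenario (b) moves both arms the same way. Scenario (c) is a label rather than a value, since (a) and (b) are themselves assumptions of the not-at-random kind. What is at stake is whether the reported range for the effect covers the uncertainty that delayed consent creates.

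**Working it through.** **Plan's own figures.** Projected quit rates section: OPT IN .30 × .29 + .70 × .10 = .157. OPT OUT .80 × .29 + .20 × .10 = .252. Both reproduce.

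**Inputs that are assumed.** The article projects these rates for whole arms; here they are applied to consenters. It plans no refusal rate, so 5% and 9% are taken from within the single-digit range mentioned in the Discussion. Equal refusal is also an assumption, relaxed in step 3.

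**1. Formulas.** Let p be the consenters' quit rate, r the refusal proportion and q the refusers' quit probability, each by arm. The arm rate is (1 - r)p + r·q. Scenario (a) sets q = 0 in both arms and (b) sets q = 1 in both. Hence

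difference under (b) - difference under (a) = r_OUT - r_IN,

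which is zero when refusal is equal.

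**2. Equal refusal.**

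| | 5% refusal | 9% refusal |
|---|---|---|
| (a) OPT IN / OPT OUT | .1492 / .2394 | .1429 / .2293 |
| (a) difference | 9.0 points | 8.6 points |
| (b) OPT IN / OPT OUT | .1992 / .2894 | .2329 / .3193 |
| (b) difference | 9.0 points | 8.6 points |
| OPT IN refusers abstinent, OPT OUT refusers smoking | .2394 - .1992 = 4.0 points | .2293 - .2329 = -0.4 points |
| OPT IN refusers smoking, OPT OUT refusers abstinent | .2894 - .1492 = 14.0 points | .3193 - .1429 = 17.6 points |

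The unfavourable extreme removes the effect when (1 - r) × .095 = r, that is at r = .095 / 1.095 = 8.7%. A milder departure does much less. At 9% refusal, refusers' abstinence 20 points higher in OPT IN than in OPT OUT lowers the difference by .09 × .20 = 1.8 points, from 8.6 to 6.8.

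**3. Unequal refusal.** With 9% in OPT IN and 5% in OPT OUT, (a) gives .2394 - .1429 = 9.7 points and (b) gives .2894 - .2329 = 5.7. With 5% and 9% the other way, (a) gives 8.0 and (b) gives 12.0. In each case the pair differs by the 4-point refusal gap and by nothing else.

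**4. Decision quantity.** P(OPT OUT better) is approximated by Φ(difference / SE), with SE² the sum of rate × (1 - rate) / n over the arms. The average arm sizes in the expected scenario are 387 in OPT OUT and 625 - 387 = 238 in OPT IN.

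| Refusal | (a) | (b) | OPT IN refusers abstinent, OPT OUT smoking |
|---|---|---|---|
| 5% | 0.9978 | 0.9954 | 0.883 |
| 9% | 0.9972 | 0.9915 | 0.459 |

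With 500 per arm, the last column is 0.938 at 5% and 0.447 at 9%. The risk ratio is .252 / .157 = 1.605 under (a). Under (b) it is .2894 / .1992 = 1.453 at 5% and .3193 / .2329 = 1.371 at 9%.

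**The case against.** A reader might infer from the equal differences that (a) and (b) test nothing. The documents do not support that. The trial decides on a posterior probability, and this moves between (a) and (b) even with equal refusal: at 9% it goes from 0.9972 to 0.9915, below the early-success threshold of .9925 though still above the .99 used for confirmation. Nor does the article assume equal refusal, and the pair does respond to a refusal gap.

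Three further points are fair. The use of one assumption in both arms is inferred, not stated. The words *pooled* and *overall* may mean consenters plus refusers within each randomized arm rather than both arms merged. And scenario (c), together with the pattern mixture or selection model named just before it, could hold arm-specific assumptions, with the parameters left to a fuller document.

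A reader might also infer that the investigators would present agreement between (a) and (b) as proof that refusal did no harm. The article says only that the analysis is exploratory and will be reported. Scenario (a) repeating the main rule is no fault in itself, since it can serve as the reference case.

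What remains is narrower. The article does list its scenarios, and neither of the two that can be computed, nor any reading of the pair, covers refusers whose outcomes differ by arm.

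**Conclusion.** The point holds as a limited one. Scenarios (a) and (b) do not bound the treatment effect, and no arm-differential case is named for the bias that consent after arm-specific treatment can introduce. With quit rates of 15.7% and 25.2% among consenters and equal refusal, the pair gives a single difference (9.0 points at 5% refusal, 8.6 at 9%), while the arm-specific extremes run from 4.0 to 14.0 and from -0.4 to 17.6.

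The extremes require every refuser in one arm to be abstinent and every refuser in the other to smoke, so they mark limits and are not forecasts. The probabilities rest on a normal approximation and on illustrative arm sizes. The primary analysis and the stopping rule are unaffected. This is an inexpensive improvement to an exploratory analysis.

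**What to change.** In the Sensitivity analyses section:

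- State that quit rates are reported by randomized arm, with the arm difference and its posterior probability.
- Keep (a) as the reference case and (b) as its counterpart.
- Define (c) as a grid in which the refusers' quit probability varies from 0 to 1 separately in each arm, including both opposite cases.
- Report the combinations at which the probability for OPT OUT falls below .99, and the refusal counts by arm.
- Say whether the pattern mixture or selection model also allows assumptions that differ by arm.

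The grid needs only the refusal counts by arm, a short program and a few sentences. The cost is a little more analysis, and the result may look less robust than under (a) and (b) alone.
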